### Statistical analysis

The analysis of the per-protocol population will be considered the primary analysis. The differences between the MA TKA and FA TKA groups will be analysed by calculating the difference from baseline per patient, and a two-sided confidence interval for the difference between the changes from baseline values will be calculated. This confidence interval will cover the true difference in the percentage change from baseline with a probability of 95%. The following statistical methods will be employed to analyse the data: descriptive statistics, independent *t* test, paired *t* test, analysis of variance, Fisher exact test, chi-square test and graphical displays. Assumptions of normality will be tested with the D’Agostino test. Assumptions of homogeneity of variance will be tested with Levene’s test. If the distributional assumptions are (severely) violated, non-parametric techniques such as the Mann–Whitney test will be employed. In the event that FA TKA is converted to MA TKA intraoperatively, analysis will be performed using the intention-to-treat population and the treatment actually received by the patients. Intraoperative conversion from FA TKA to MA TKA will be documented and presented and published as part of the study. Statistical significance is set at a *P* value <0.05 for all analyses and all statistical analyses will be performed using SPSS software version 25 (SPSS Inc., Chicago, IL, USA). The Bonferroni correction will be used to adjust *P* values to reduce the risk of type I error with performing multiple statistical comparisons.

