**Methods and analysis:**

This prospective double-blinded randomised control trial will include 100 patients with symptomatic knee osteoarthritis undergoing primary robotic arm-assisted TKA. Following informed consent, patients will be randomised to MA TKA (the control group) or FA TKA (the investigation group) at a ratio of 1:1 using an online random number generator. Blinded observers will review patients at regular intervals for 2 years after surgery to record predefined study outcomes relating to postoperative rehabilitation, clinical progress, functional outcomes, accuracy of implant positioning and limb alignment, gait, implant stability, cost-effectiveness, and complications. A superiority study design will be used to evaluate whether FA TKA provides superior outcomes compared to MA TKA. Primary and secondary objectives will be used to quantify and draw inferences on differences in the efficacy of treatment between the two groups. Intention-to-treat and per-protocol population analysis will be undertaken. The following statistical methods will be employed to analyse the data: descriptive statistics, independent *t* test, paired *t* test, analysis of variance, Fisher exact test, chi-square test, and graphical displays. Ethical approval was obtained from the London-Surrey Research Ethics Committee, UK. The study is sponsored by University College London, UK.

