### Allocation

After informed consent has been obtained, the research physiotherapist will randomise the patient into one of the two groups using an online random number generator (www.random.org). A number from 1 to 100 will be randomly generated and will allocate a patient to one of the two arms of the study: 1–50 inclusive for the control group, 51–100 inclusive for the investigation group. The research physiotherapist will perform the randomisation procedure and store the designated treatment group for each patient on a password-encrypted file on the hospital computer. The operating surgeon will have this information communicated to him on the morning of surgery.

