In patients undergoing FA TKA, implants will be positioned to optimise soft tissue tension through achieving balanced flexion-extension gaps and equal mediolateral soft tissue tension by altering bone resections and implant positions rather than through soft tissue releases. This will be achieved when possible within strict alignment limits, and where not achievable because of the magnitude of a fixed deformity by balancing after bone cuts with limited soft tissue releases. The preoperative surgical plan will be used to fix a specific point on the tibia and the gaps balanced to restore the obliquity of the native joint line. In the coronal plane, femoral implant positioning will be modified from a starting point of 0° to the mechanical axis to balance the extension gap. In the sagittal plane, femoral component positioning will be set to optimise component sizing while avoiding notching by flexing up to 5°. In the axial plane, the femoral component will be aligned to the surgical transepicondylar axis and modified by up to 3° to balance the flexion gap. The size of the femoral implant will be selected using posterior referencing with the smallest size that does not overhang the femur, notch the anterior femur, or overhang mediolateral bone edges, and avoids overstuffing the patellofemoral joint. The femoral implant will be positioned at the centre of the mediolateral cortical bone edges, favouring a lateral position if necessary. In the coronal plane, tibial implant position will be aligned to the tibial mechanical axis and then modified to balance flexion and extension gaps by up to 3° of varus. Valgus tibial position will be avoided. In the sagittal plane, tibial implant position will be set to match the patient’s native posterior tibial slope, modified to balance the flexion gap if necessary. In the axial plane, the tibial implant will be positioned using Akagi’s line [2, 3, 45]. Tibial implant size will be selected with the largest size that does not overhang the anteroposterior and mediolateral bone coverage while achieving the correct rotation. The implant will be positioned in the centre between the anteroposterior and mediolateral cortical bone edges.

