### End-of-protocol treatment

Reasons for going off study protocol include:
Completion of last follow-up visit 2 years after surgeryPatient non-compliance or withdrawal (the reason for discontinuation will be recorded in the case report form)Intercurrent death

All patients included in this study are free to withdraw from the study at any time without compromise to their future treatment. On withdrawal, patients will revert to the standard follow-up regimen for routine (non-study) TKA at the study site. The end-of-study form will be completed and the reason for withdrawal documented. This form will also be completed if the patient is lost to follow-up or dies during the course of the study. Data to the point of discontinuation will be used for analysis.

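### A superiority trial makes the per-protocol population primary, and its rule for FA-to-MA conversion leaves unclear which analysis decides the result

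*Protocol article*

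**What the plan says.** The Abstract (Methods and analysis) fixes the aim: "A superiority study design will be used to evaluate whether FA TKA provides superior outcomes compared to MA TKA". It then lists two populations without ranking them: "Intention-to-treat and per-protocol population analysis will be undertaken".

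The Statistical analysis section ranks them, without condition: "The analysis of the per-protocol population will be considered the primary analysis". Later in the same section comes a rule for one event, intraoperative conversion from FA to MA: "analysis will be performed using the intention-to-treat population and the treatment actually received by the patients". Conversion in that direction is also to be reported: "Intraoperative conversion from FA TKA to MA TKA will be documented and presented and published as part of the study". No conversion from MA to FA is mentioned.

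Two other places bear on the point. Under Allocation, the surgeon learns the arm before operating: "The operating surgeon will have this information communicated to him on the morning of surgery". Under Surgical intervention, the FA technique has its own provision for knees that cannot be balanced within the alignment limits: "where not achievable because of the magnitude of a fixed deformity by balancing after bone cuts with limited soft tissue releases".

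**The concern.** In a superiority trial, the reason to attribute a difference to treatment is that the groups compared are those that randomisation formed. A per-protocol primary analysis gives that up, because membership then depends on what happened after allocation. Here at least one such event is decided in theatre by someone who knows the arm. Blinding of patients and outcome observers does not protect against selection at that step.

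The conversion rule adds a second difficulty. If a knee is converted, the section offers per-protocol (named primary), intention to treat and treatment received, and does not say which one carries the primary conclusion. The choice could then be made after the results are known. Treatment received is no remedy: it takes the converted knees out of FA and also places them in MA.

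**Working it through.** The plan gives no conversion rate, no outcome gap for converted knees and no estimate of bias, so there is no stated figure to reproduce. What follows shows the direction and possible size under stated assumptions.

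**Inputs from the protocol (Sample size section)**
- Standard deviations of the 2-year WOMAC: 22.6 and 20.3. Pooled: √[(22.6² + 20.3²)/2] = 21.48.
- Target difference: 11 points.
- 100 patients, 10% drop-out, 1:1 allocation: 100 × 0.9 / 2 = 45 evaluable per arm.

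**Assumptions (not in the documents)**
- A share c of knees is of the kind that would be converted if allocated to FA. Randomisation puts the same share in both arms.
- These knees end g points worse than the others, whichever alignment they receive.
- There is no true difference between FA and MA.

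**Bias under each analysis.** Let the other knees have mean m.
- Intention to treat: both arms have mean m + cg. Bias = 0.
- Per-protocol, with converted knees excluded: FA has mean m and MA has m + cg. Bias toward FA = c × g.
- Treatment received: FA has mean m. MA holds its own share c of such knees plus those moved from FA, giving m + 2cg/(1 + c). Bias toward FA = 2cg/(1 + c).

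| c | g | Per-protocol bias | Treatment-received bias |
|---|---|---|---|
| 5% | 10 | 0.5 | 1.0/1.05 = 0.95 |
| 10% | 10 | 1.0 | 2.0/1.10 = 1.82 |
| 10% | 20 | 2.0 | 4.0/1.10 = 3.64 |
| 15% | 20 | 3.0 | 6.0/1.15 = 5.22 |

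The per-protocol figures run from 0.5/11 = 5% to 3/11 = 27% of the target difference.

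**Effect on the error rate.** Take 45 MA and about 40 FA patients after exclusions. SE = 21.48 × √(1/45 + 1/40) = 4.67. The chance of wrongly declaring FA better is P(Z > 1.96 − bias/SE), nominally 2.5%:
- bias 1 point: P(Z > 1.746) = 4.0%
- bias 2 points: P(Z > 1.532) = 6.3%
- bias 3 points: P(Z > 1.317) = 9.4%

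**Opposite sign.** If convertible knees do better on the analysed scale, g is negative. With c = 10% and g = −10 the per-protocol bias is 1.0 point against FA, and the treatment-received bias 1.82 points against FA.

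**Limit of the calculation.** The standard deviation is that of 2-year scores, whereas the section analyses change from baseline, for which no standard deviation is given. The error rates are therefore illustrative; the bias formulas do not depend on it.

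**The case against.** Four things can be said for the plan, and most of them stand as limits on the point.

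*Converted knees are not expressly excluded.* A reader might infer that difficult knees will be dropped from the FA arm. The text does not say so. For this very event it prescribes intention to treat and treatment received. On one natural reading that specific rule overrides the general one, and intention to treat keeps the converted knees in FA. This stands as a possible reading, but the section does not state it, and intention to treat is nowhere called primary.

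*Some difficult knees need not be converted.* Fixed deformities can be handled inside the FA technique with limited releases, and conversions must be documented and published. This lowers the likely conversion rate and makes conversions visible. It does not remove them, since the section provides for them.

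*The direction is not settled.* A reader might infer a bias toward FA. That requires converted knees to do worse on change from baseline, where patients who start worse may have more room to improve. Exclusions for withdrawal or non-compliance can also occur in either arm. The documents support a comparison unprotected by randomisation, not a known direction of bias.

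*The size is modest under the assumptions.* Biases of 0.5 to 3 points compare with about 1.96 × 4.67 = 9.2 points needed for significance. The claim that a positive result could not be attributed to FA would go too far.

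A reader might also see a conflict with the End-of-protocol treatment section, which says "Data to the point of discontinuation will be used for analysis". There is none: WOMAC is also collected at 6 weeks, 6 months and 1 year, where such data can be used, and a 2-year t test by intention to treat would lose the same patients.

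**Conclusion.** The point holds in this form. The protocol fixes a per-protocol primary analysis for a superiority claim, so the primary comparison can exclude patients on post-randomisation events, including a conversion decided with knowledge of the arm. The Statistical analysis section also leaves open which analysis decides the result once a conversion has occurred. Both follow from the text alone.

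The size does not. It rests on an assumed conversion share of 5–15% and an outcome gap of 10–20 points, which together give roughly 0.5 to 3 WOMAC points under per-protocol and more under treatment received. The sign depends on whether converted knees do worse or better on the analysed scale. One-sided exclusion in favour of FA is a possibility that the wording permits; the plan does not prescribe it.

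The correction should still be made, because it concerns the population behind the primary conclusion.

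**What to change.** In the Statistical analysis section, replace the sentence that names the primary population with wording to this effect: the primary analysis is by intention to treat and includes all randomised patients in the arm to which they were allocated, whatever alignment was executed.

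Then:
- make per-protocol a sensitivity analysis, with deviations defined the same way in both arms and conversion in either direction covered;
- keep the treatment-received analysis as descriptive only;
- reword the conversion sentence so that it agrees with this order, and rank the populations the same way in the Abstract.

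This changes wording only; no data collection or sample size changes. The price is slight dilution if conversions occur. If converted patients gain nothing from FA and the true difference is 11 points for everyone else, the intention-to-treat contrast is 11 × (1 − c): 10.45 points at 5% converted, 9.9 at 10% and 9.35 at 15%.

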## Methods/design

### Objectives

The primary objective of this study is to compare the total Western Ontario and McMaster Universities Arthritis Index (WOMAC) score in MA TKA versus FA TKA at 2 years after surgery. As FA TKA enables improved restoration of native, patient-specific knee kinematics [15, 26, 29], the study hypothesis is that total WOMAC scores will be superior in patients undergoing FA TKA compared to MA TKA at 2 years follow-up.

The secondary objectives are to compare the following outcomes between the two treatment groups:
Accuracy of implant positioning and limb alignmentSurgical efficiencyPostoperative functional rehabilitationFunctional outcomesQuality of lifeImplant migrationGaitResource use and cost-effectivenessComplications

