### Outcomes

All study patients will undergo review by two blinded observers (one orthopaedic registrar and one clinical research fellow) at 2 weeks, 6 weeks, 6 months, 1 year and 2 years following surgery. During these follow-up times, predefined clinical, functional and radiological outcomes will be recorded by these observers using case report forms. The following outcomes will be recorded in all study patients:
Accuracy of implant positioning and limb alignment as assessed using CT scans of the knee joint performed postoperatively at 6 weeks.Operating time (minutes)Time to hospital discharge (hours)Analgesia requirements during inpatient admission and postoperatively at 6 weeks, 6 months, 1 year and 2 yearsPatient-reported outcome measures including Forgotten Joint Score (FJS), Oxford Knee Score (OKS), short-form health survey of 12 items (SF-12), Knee Injury and Osteoarthritis Outcome Score (KOOS), WOMAC, University of California at Los Angeles score and University College Hospital functional knee score preoperatively and postoperatively at 6 weeks, 6 months, 1 year and 2 yearsHealth-related quality of life as measured using the European Quality of Life questionnaire with five dimensions for adults (EQ-5D) preoperatively and postoperatively at 6 weeks, 6 months, 1 year and 2 yearsMobilisation distance (metres) and use of mobility aids during inpatient admission and postoperatively at 6 weeks, 6 months, 1 year and 2 yearsRange of movement (degrees) in knee joint during inpatient admission and postoperatively at 6 weeks, 6 months, 1 year and 2 yearsFemoral and tibial implant early migration as assessed using RSA performed postoperatively at 2 weeks, 6 weeks, 6 months, 1 year, and 2 yearsGait analysis performed postoperatively at 6 months and 1 year using an instrumented treadmill with force platesResource use and cost-effectiveness, including comparisons between the two treatment groups relating to operating time, theatre efficiency, equipment and sterilisation costs, analgesia requirements, inpatient rehabilitation, time to discharge, outpatient follow-up, additional imaging costs and need for further surgery.Complications

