### Sample size

Using data from a previous study recording functional outcomes, the mean WOMAC score at 2 years using MA TKA was 26 (standard deviation 22.6) and using TKA with kinematic alignment was 15 (standard deviation 20.3) [14]. Using a two-tailed, two-sample *t* test with an effect size of 0.35, power of 90% with significance level of 5%, and accounting for an expected drop-out rate of 10% during the 2-year follow-up period, the study requires 100 patients to detect a minimal clinically important difference of 11 points in the total WOMAC score between the two treatment groups [13].

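### The group comparison uses unadjusted change from baseline, with an undefined normality gate to Mann–Whitney, although one pre-specified baseline-adjusted model would use data already collected

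*Protocol article*

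**What the plan says.** All references are to the protocol article.

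- **Objectives.** The primary aim is to "compare the total Western Ontario and McMaster Universities Arthritis Index (WOMAC) score in MA TKA versus FA TKA at 2 years after surgery".
- **Sample size.** A two-sample t test on 2-year scores: "the mean WOMAC score at 2 years using MA TKA was 26 (standard deviation 22.6"), against 15 (SD 20.3) for kinematic alignment. The target is 11 points with 90% power, two-sided 5%, 10% drop-out and 100 patients.
- **Statistical analysis, scale.** Group differences "will be analysed by calculating the difference from baseline per patient". On how the result will be reported, the section states that "a two-sided confidence interval for the difference between the changes from baseline values will be calculated". The next sentence describes that interval as one for the percentage change. The listed methods include independent and paired t tests and analysis of variance, but no baseline-adjusted model.
- **Statistical analysis, gate.** "Assumptions of normality will be tested with the" D'Agostino test, and equality of variances with Levene's test. "If the distributional assumptions are (severely) violated, non-parametric techniques such as the" Mann–Whitney test are to be used. No threshold is given.
- **Outcomes.** Baseline WOMAC is available, since the list of patient-reported measures includes "WOMAC, University of California at Los Angeles score and University College Hospital functional knee score preoperatively and postoperatively at 6 weeks, 6 months", then at 1 and 2 years.

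**The concern.** There are two linked weaknesses in what the section fixes.

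First, the objective and the sample size are on the 2-year score, while the analysis subtracts baseline. Subtraction forces a coefficient of 1 on baseline. If the true slope is well below 1, it adds noise. A model that estimates the slope avoids this at the cost of one degree of freedom.

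Second, the test depends on a preliminary look at the outcome distribution, with a trigger that two analysts could apply differently. Mann–Whitney does not test the difference in mean points on which the trial is sized and for which the confidence interval is promised. The P value and the interval could therefore answer different questions.

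At stake are precision for the primary comparison and a primary test that is not fixed before the outcome data are seen.

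**Working it through.** **Inputs from the protocol.** Difference 11 points; SDs 22.6 and 20.3; two-sided 5%; 100 patients at 1:1 with 10% drop-out, so 45 evaluable per arm.

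**Assumed, not in the documents.** The baseline to 2-year correlation r, and k, the ratio of baseline SD to 2-year SD. Ranges are shown.

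**Step 1: the plan's own figure.** Common SD = √[(22.6² + 20.3²)/2] = √461.4 = 21.48. Standardised difference d = 11/21.48 = 0.512. With 45 per arm the noncentrality is 0.512 × √(45/2) = 2.43 on 88 degrees of freedom, which gives 67% power for the 2-year score alone. The stated 90% is not reproduced. That is a separate problem; 67% serves here only as the reference.

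**Step 2: variance factors relative to the 2-year score.**

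- Change score: 1 + k² − 2rk, which is 2(1 − r) when k = 1.
- ANCOVA: 1 − r².
- Change minus ANCOVA: (k − r)², which is never negative and is zero when r = k, that is, when the slope r/k equals 1.
- Change is worse than the 2-year score alone only if k² − 2rk > 0, that is, r < k/2.

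**Step 3: power with equal SDs (k = 1), using d/√(variance factor), noncentral t.**

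| r | Change factor | ANCOVA factor | Power, change | Power, ANCOVA |
|---|---|---|---|---|
| 0.2 | 1.60 | 0.96 | 48% | 69% |
| 0.3 | 1.40 | 0.91 | 53% | 71% |
| 0.4 | 1.20 | 0.84 | 59% | 75% |
| 0.5 | 1.00 | 0.75 | 67% | 79% |
| 0.6 | 0.80 | 0.64 | 77% | 85% |
| 0.7 | 0.60 | 0.51 | 87% | 92% |

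The 2-year score alone stays at 67% throughout.

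**Step 4: unequal SDs, change versus ANCOVA.**

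| k | r | Power, change | Power, ANCOVA |
|---|---|---|---|
| 0.6 | 0.3 | 67% | 71% |
| 0.6 | 0.6 | 85% | 85% |
| 0.8 | 0.3 | 61% | 71% |
| 1.2 | 0.3 | 45% | 71% |

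**Step 5: the gate.** A simulation used 4,000 trials per setting and 45 per arm. It switched from the t test on change to Mann–Whitney when the D'Agostino test gave P < 0.05 in either arm. That cut-off and the skewed shape are assumptions, and Levene's test was not included.

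- Switch rate: about 10% with normal data, 45–50% with skewed 2-year scores.
- Type I error of the two-stage rule: 4.6–5.7%.
- Power, two-stage versus ANCOVA, normal data: 52% versus 69% (r = 0.3) and 68% versus 79% (r = 0.5).
- Power, two-stage versus ANCOVA, skewed data: 54% versus 71% and 66% versus 77%.

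**The case against.** **The change score is valid.** In a randomised comparison it is unbiased, so this is a matter of efficiency. That stands.

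**The change score need not lose power.** A reader might infer that subtracting baseline always lowers power below the 2-year score. The documents do not support that, because they give neither r nor the baseline SD. With equal SDs, change is level with the 2-year score at r = 0.5 and better above it. What remains is the comparison with ANCOVA, whose advantage shrinks to about 5 points at r = 0.7 and vanishes where the slope is 1.

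**A switch is not a foregone conclusion.** A normal curve with mean 15 and SD 20.3 would put 23% of patients below zero. A reader who takes the score as bounded at zero might conclude that a switch is almost certain. But those figures describe 2-year scores, whereas the analysed variable is change. The trigger is also severe violation, not a significant D'Agostino test. The simulated 45–50% shows that a switch is a real prospect under skew, no more.

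**Type I error.** A reader might infer that the pre-test inflates it. The simulation shows no meaningful inflation.

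**The interval may survive the switch.** The text promises a confidence interval for the difference in changes and does not make it conditional on the pre-test. That is a fair reading, but it leaves a rank-based P value beside a mean-based interval.

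**This belongs in an analysis plan.** The section lists methods for all outcomes and never names the WOMAC test in one sentence; the t test is inferred from the change-score wording and the sample-size section. Exact thresholds could well sit elsewhere. But the article itself states the change score and the gate, so a separate plan would have to replace that text, not merely add to it.

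**Conclusion.** The point holds as an avoidable loss of precision and an unfixed choice of test, not as a flaw in validity. ANCOVA on the 2-year score is never materially worse than the stated analysis. With equal SDs it gains about 21 percentage points of power at r = 0.2, 12 at r = 0.5 and 5 at r = 0.7. At an SD ratio of 0.6 with r = 0.6 it gains nothing. These sizes rest on assumed r and k, 45 evaluable per arm, and the protocol's own SDs and 11-point difference. The existence of the mismatch, and the undefined trigger, rest on the text alone.

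A reader might also infer that ANCOVA repairs the sample size. It does not: with these SDs and 45 per arm it reaches 90% only if r is about 0.68 or more. The shortfall against the stated 90% needs its own answer.

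**What to change.** 1. Name one primary model: 2-year total WOMAC regressed on arm and preoperative WOMAC, reporting the adjusted difference in points with a heteroscedasticity-robust or bootstrap 95% confidence interval.
2. Remove the D'Agostino and Levene gate for the primary endpoint. The robust or bootstrap interval covers the concern that the gate was meant to address.
3. Keep a rank-based test as a fixed sensitivity analysis, reported whatever the distribution looks like.
4. Reconcile the 2-year score, change and percentage-change wording to one scale across the Objectives, Sample size and Statistical analysis sections.

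The cost is wording only. Preoperative WOMAC is already collected, the named software can fit the model, and no visit, measurement or patient is added. The change should be dated before 2-year outcomes are examined by arm.

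### The 95% confidence interval is specified in points but said to cover a percentage change, and the protocol does not say whether the 2-year score or the change from baseline decides the trial

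*Protocol article*

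**What the plan says.** Three places in the protocol article bear on the primary effect.

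- **Objectives.** The primary objective is to "compare the total Western Ontario and McMaster Universities Arthritis Index (WOMAC) score in MA TKA versus FA TKA at 2 years after surgery". The hypothesis is likewise about the score at that time: "total WOMAC scores will be superior in patients undergoing FA TKA compared to MA TKA at 2 years follow-up".
- **Sample size.** The inputs are 2-year scores: "the mean WOMAC score at 2 years using MA TKA was 26 (standard deviation 22.6") against 15 (SD 20.3) with kinematic alignment. The trial is sized for a "minimal clinically important difference of 11 points in the total WOMAC score".
- **Statistical analysis.** Group differences "will be analysed by calculating the difference from baseline per patient". To compare the arms, the section then specifies that "a two-sided confidence interval for the difference between the changes from baseline values will be calculated". The next sentence reads "This confidence interval will cover the true difference in the percentage change from baseline with a probability of 95" per cent. The same section makes the per-protocol population primary.

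No formula for percentage change appears, and no other sentence mentions it. The Outcomes section shows that WOMAC is collected before surgery as well as at 2 years.

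**The concern.** There are two problems, of different weight.

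The first is a false statement. The interval described is for a difference in points, but the coverage claimed for it concerns a difference in percentages. These are different parameters in different units, so the 95% does not carry over from one to the other.

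The second is an open choice. The objective and the sample size refer to the 2-year score, and the analysis refers to the change from baseline. Both are in points, but they give different standard errors and P values from the same data. With significance set at P < 0.05 and neither named as primary, the conclusion could depend on a choice made after the results are known.

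**Working it through.** **Inputs from the protocol article.** 2-year means 26 and 15, SDs 22.6 and 20.3, 100 patients, 1:1 allocation, 10% drop-out. Hence 50 × 0.9 = 45 evaluable per arm. The 11 points reproduce as 26 − 15. (The total of 100 does not follow from 11 points, these SDs, 90% power and a two-sided 5% test, but that is a separate matter and is not used here.)

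**Inputs assumed, because the protocol gives none.** Baseline mean, baseline SD, and the correlation ρ between baseline and 2-year score.

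**Step 1: what each measure estimates.** Let B be the baseline and Y the 2-year score.

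- Difference in score: E[Y | FA] − E[Y | MA] = 15 − 26 = −11 points.
- Difference in change: E[Y − B | FA] − E[Y − B | MA] = −11 − (E[B | FA] − E[B | MA]). Randomisation makes the bracket zero, so this is also −11 points.
- Difference in percentage change: 100 × (E[Y/B | FA] − E[Y/B | MA]). If every patient had the same baseline b, this would be 100 × (−11)/b.

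| Common baseline b (assumed) | 40 | 50 | 60 | 70 |
|---|---|---|---|---|
| Difference, points | −11 | −11 | −11 | −11 |
| Difference, percentage points | −27.5 | −22.0 | −18.3 | −15.7 |

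The first two measures share a target and the third does not.

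**Step 2: coverage of the interval described.** Simulation with 45 per arm and 4,000 runs per row. Scores were normal with the protocol's 2-year means and SDs, ρ = 0.3, and baseline values were floored at 10. The interval is the 95% interval for the difference in change, in points.

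| Baseline mean (SD), assumed | True % difference | Coverage of points difference | Coverage of % difference |
|---|---|---|---|
| 40 (12) | −30.2 | 94.7% | 1.4% |
| 40 (18) | −34.1 | 94.9% | 0.3% |
| 50 (12) | −23.2 | 95.4% | 22.4% |
| 50 (18) | −25.6 | 95.2% | 16.3% |
| 60 (12) | −18.9 | 95.2% | 59.0% |
| 60 (18) | −20.2 | 95.6% | 55.1% |
| 70 (12) | −16.0 | 95.3% | 79.5% |
| 70 (18) | −16.7 | 95.0% | 78.6% |

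Hand check of the 50 (12) row:

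- Variance of change, MA: 22.6² + 12² − 2(0.3)(22.6)(12) = 492.0.
- Variance of change, FA: 20.3² + 12² − 2(0.3)(20.3)(12) = 409.9.
- SE = √((492.0 + 409.9)/45) = 4.48, and half-width = 1.987 × 4.48 = 8.90.
- The percentage target lies 23.2 − 11.0 = 12.2 from the centre of the interval, so coverage ≈ Φ((8.90 − 12.2)/4.48) ≈ 0.23, against 22.4% simulated.

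**Step 3: why naming one points measure matters.** Pooled 2-year SD = √((22.6² + 20.3²)/2) = 21.48. With equal baseline SD (assumed), the SD of change is 21.48 × √(2(1 − ρ)), and the residual SD after adjusting for baseline is 21.48 × √(1 − ρ²). Power for 11 points is Φ(11/(SD × √(2/45)) − 1.96).

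| ρ (assumed) | SD of change | Power, 2-year score | Power, change | Residual SD, adjusted | Power, adjusted |
|---|---|---|---|---|---|
| 0 | 30.38 | 68% | 40% | 21.48 | 68% |
| 0.3 | 25.42 | 68% | 54% | 20.49 | 72% |
| 0.5 | 21.48 | 68% | 68% | 18.60 | 80% |
| 0.7 | 16.64 | 68% | 88% | 15.34 | 93% |

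Score and change swap places at ρ = 0.5. In this approximation the adjusted analysis is never worse than either.

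**The case against.** The strongest reply is that the percentage sentence is a drafting slip. The protocol orders a per-patient difference from baseline and an interval for the difference between those changes. It never orders a percentage analysis, gives a formula for one or sizes the trial on one. That stands as a reading of intent: a reader might infer that success could be declared on percentage change, but the text gives little support for that. The sentence is still false as written, and nothing elsewhere corrects it.

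Four other inferences go further than the document allows.

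- *The primary effect is defined in three incompatible ways.* Step 1 shows that score and absolute change share one target under 1:1 randomisation. Only percentage change is a different quantity. The equality is, however, not assured in the per-protocol set, where exclusions after randomisation can unbalance baseline.
- *The interval can never cover the percentage difference.* It can do so by chance, and if the two arms have identical distributions both differences are zero and coverage is nominal.
- *The sample size does not apply to change.* Eleven points of score is eleven points of change, and only the SD moves. With a baseline SD of 17 and ρ = 0.4 (both assumed), the SD of change is √(17² + 21.48² − 2(0.4)(17)(21.48)) = 21.4, practically the 21.48 of the score itself.
- *The interval should be judged against 11 points.* The protocol uses 11 points only for sizing and states superiority at P < 0.05, so that would be a new criterion.

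It is also fair to say that covariate adjustment is commonly left to an analysis plan, which is not shown. Baseline adjustment is therefore offered as the preferred way to settle the choice. Its absence from the article is not counted as an error.

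**Conclusion.** The point holds in two parts.

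1. The coverage statement is wrong. In the scenarios tried, the interval described covered the percentage difference in about 0.3% to 79% of runs. These figures rest on assumed baseline means of 40 to 70, SDs of 12 to 18, ρ = 0.3 and normal scores. Their exact size would change with other inputs. That the claim fails in general does not depend on them, because the two parameters differ.
2. The deciding measure is not named. Score and change from baseline aim at the same 11 points, but power at 45 per arm is about 68% for the score and anywhere from 40% to 88% for change as ρ goes from 0 to 0.7, assuming equal baseline SD. P values from the two can fall on opposite sides of 0.05. This is an ambiguity between two estimators of one quantity, with the caveat already given for the per-protocol set.

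**What to change.** Before outcome data are analysed:

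- Delete the percentage-change sentence, or reword it so that the 95% refers to the between-arm difference in points.
- Name one primary effect measure in the objective, the sample size and the analysis alike. The preferred choice is the between-arm difference in total WOMAC at 2 years, adjusted for baseline WOMAC, with a two-sided 95% confidence interval. Adjustment also deals with measured baseline imbalance in WOMAC, though not with other effects of excluding patients after randomisation.
- If percentage change is wanted, define it and list it as descriptive only.

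The cost is a few sentences of protocol or analysis-plan wording. Baseline WOMAC is already collected, so no visit, form or patient is added.
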